## Abstract

Recently, the VALENF instrument, Nursing Assessment by its acronym in Spanish, was developed as a meta-tool composed of only seven items with a more parsimonious approach for nursing assessment in adult hospitalization units. This meta-tool integrates the assessment of functional capacity, the risk of pressure injuries and the risk of falls. The general objective of this project is to validate the VALENF instrument by studying its diagnostic accuracy against the instruments commonly used in nursing to assess functional capacity, the risk of pressure injuries and the risk of falls. An observational, longitudinal, prospective study is presented, with recruitment and random selection based on admissions to six adult hospitalization units of the Hospital Universitario de La Plana. The study population will be made up of patients hospitalized in these units. The inclusion criteria will be patients over 18 years of age with a nursing assessment within the first 24 h of admission and an expected length of stay greater than 48 h and who sign the informed consent form. The exclusion criteria will be transfers from other units or centers. A sample of 521 participants is estimated as necessary. The evaluation test will be the VALENF instrument, and the reference tests will be the Barthel, Braden and Downton indices. Sociodemographic variables related to the care process and results such as functional loss, falls or pressure injuries will be collected. The evolution of functional capacity, the risk of falls and the risk of pressure injuries will be analyzed. The sensitivity, specificity and positive predictive values of the VALENF instrument will be calculated and compared to those of the usual instruments. A survival analysis will be performed for pressure injuries, falls and patients with functional loss. The VALENF instrument is expected to have at least the same diagnostic validity as the original instruments.

**Trial registration** The study will be retrospectively registered (ISRCTN 17699562, 25/07/2023).

## Background

Nurses who work in hospitalization units are responsible for evaluating, planning, executing and reassessing the care that patients require throughout the care process and documenting all of this in the clinical history. However, this group perceives health documentation as an administrative burden due to the increase in the amount of data and the duplication of elements [1]. Moreover, the implementation of electronic health records has prolonged data recording times, increased workloads [2, 3], and reduced direct care times [4] and has made nursing assessments incomplete, inconsistent, and inaccurate [5].

Nursing assessment is defined as a planned, systematic, continuous, and deliberate process of collecting, classifying, and categorizing individualized information to recognize individuals' responses to their actual or potential health problems and needs [6]. These assessments are the basis for making nursing diagnoses and carrying out interventions adjusted to the patient’s needs [7]. Therefore, any error, lack of information or the use of instruments with little validity or reliability can affect the next steps in the nursing process and result in fragmented and incomplete care with repercussions on the quality of care and the development of adverse effects [8].

Some factors that could justify nurses perceiving nursing assessment as an administrative burden [9] include increased patient complexity and a heavy workload [10], the use of different standardized nursing languages [11], and electronic medical records developed according to the paper format and without considering the opinions of nurses [12]. All this leads to a greater amount of data and duplicate items and a diversity of evaluation instruments [1].

Different studies have shown that nursing assessments do not meet adequate standards of quantity or quality of information [13–15], including studies that have analyzed the completion of information on functional capacity, falls or pressure injuries [12, 16–18]. In fact, these instruments are probably the most commonly used by nurses in adult hospitalization units. These instruments are used independently, but they share constructs, dimensions, and items related to mobility, hygiene, eating, or elimination [19, 20], which implies that their items become redundant and are duplicated [1]. The use of redundant assessment instruments generates skepticism and a perception of wasting time, making it difficult for them to be accepted and implemented in nursing [21]. Therefore, nursing assessments can become an automatic and imprecise task without much input from nurses, affecting not only their validity but also the task of detecting patients at risk [22].

Recently, the “VALoración ENFermera” (VALENF) instrument, Nursing Assessment by its acronym in Spanish, was developed as a meta-tool composed of only 7 items with a more parsimonious approach for nursing assessment in adult hospitalization units [23, 24]. This meta-tool integrates the assessment of functional capacity, the risk of pressure injuries and the risk of falls. Thus, the VALENF instrument has a high predictive capacity on the Barthel (R^2^adj = 0.938), Braden (R^2^adj = 0.926) and Downton (R^2^adj = 0.921) indices, with high interobserver reliability (ICC > 0.9) and good construct validity (RMSEA = 0.0726; TLI = 0.968) and internal consistency (Ω = 0.864), although its sensitivity, specificity, and predictive values for detecting patients at risk of functional loss, pressure injuries, or falls remain to be determined. Consequently, the main objective of this project is to study the diagnostic accuracy of the VALENF instrument compared to instruments commonly used in nursing in adult hospitalization units to assess functional capacity, the risk of pressure injuries, and the risk of falls.

## Methods/design

### Design

An observational, longitudinal, prospective study with recruitment and random selection of hospitalized patients is presented to estimate the diagnostic accuracy of a meta-tool that collapses other instruments for assessing functional capacity and the risk of pressure injuries and falls in a public hospital in the province of Castellón. The study began in January 2023 and will end in December 2024. Figure 1 presents a general timeline of the study.

**Fig. 1 Fig1:**

Timeline of the study

### Participants and sample

The study population will be made up of patients admitted to the adult hospitalization units of the Hospital Universitario de La Plana. Special service units (intensive care, emergency, operating room and resuscitation), home hospitalization units and maternal-infant and obstetric-gynecological hospitalization units will not be part of the study. Patients over 18 years of age who are assessed in the first 24 h after admission to the hospitalization unit using the Barthel Index, Braden Index, Downton scale and VALENF instrument, are expected to stay longer than 48 h, and who agree to participate in the study and sign the informed consent form will be included in the study. Patients who are transferred from other units of the same hospital and other hospitals will be excluded since their care process is in progress and their assessment on admission does not correspond to the initial assessment after admission.

The sample size was calculated with Epidata v4 and was based on a comparison of proportions for paired data, since the condition of the patient will be unknown at the time of the evaluations, and the reference tests will be used for all subjects. A confidence level of 95%, an accuracy of 80% and a replacement rate of 10% were considered. Thus, the sample size includes 521 participants who will be stratified considering the monthly mean number of discharges from each hospitalization unit (Table 1).

**Table 1 Tab1:** Sample size estimation

Unit	Discharges in 2019	Mean monthly discharges	Estimated n (8 months)
Trauma 1A – A&E	2023	169	115
Gynecological surgery 1B	1303	109	75
Cardiology-Digestion 1D	1751	146	100
Neurology-Pneumology 2A	1550	129	89
Surgery 2B	1397	116	79
Internal Medicine 2D	1101	92	63
**Total sample**	9125	760	521

### Variables and instruments

The study includes sociodemographic variables (age and sex); variables related to the care process, such as hospitalization unit, type of process (medical, surgical), type of admission (scheduled, urgent), main diagnosis, Charlson Comorbidity Index [25, 26], pressure injury on admission (yes, no), and admission motivated by fall (yes, no); outcome variables that necessitate nursing care, such as falls, pressure injuries, and functional loss [27]; the test to be evaluated (VALENF instrument) and the reference tests (Barthel Index [28], Braden Index [29] and Downton scale [30]).

### Training of nurses

Before starting data collection, the nurses responsible for carrying out measurements will receive training to guarantee homogeneity in data collection. This training program aims to equip them with the necessary skills to use the software used in data collection and standardize patient measurements. To achieve this, several meetings will be held with nurses who voluntarily choose to participate in data collection. During these meetings, the project will be explained in detail, presenting the objectives, participant selection criteria and measurement instruments, as well as the recruitment flow and monitoring of participants during hospitalization. At the end of the training, nurses will be provided with a notebook with the necessary information to serve as a reference at any time during data collection.

### Data collection

Initially, data collection will take place between October 2023 and May 2024 using Research Electronic Data Capture (REDCap) software. Sociodemographic variables and variables related to the care process will be collected only upon admission. Moreover, the test under evaluation (VALENF instrument) and the reference tests (Barthel Index, Braden Index, and Downton scale) will be employed upon admission, every five days, and upon discharge. Finally, the outcome variables sensitive to nursing care will be collected at the time of discharge.

Nurses who work in the hospitalization units that will participate in the study will carry out the recruitment, data collection and follow-up during the hospitalization of the patients included in the study prospectively.

The recruitment procedure will begin when a patient is admitted to one of the participating hospitalization units, as long as one of the nurses participating in the study is on their work shift during the first 24 h after entry. To randomize the recruitment of the participants, a list of random numbers will be generated for each unit, and a box will be prepared with opaque envelopes with included/not included cards. The nurse who conducts the recruitment will explain the project and request informed consent (IC). The patients will be assessed upon admission, at five days, and upon discharge (Fig. 2).

**Fig. 2 Fig2:**
[figure not shown]
Flow chart with the procedure for recruiting and hospitalization follow-up participants

### Statistical analysis and diagnostic accuracy

First, a descriptive analysis of the sample will be carried out based on the nature of the variables, and whether there are significant differences in the results of the nursing assessments in terms of the hospitalization units, the type of process (medical or surgical), type of admission (urgent or programmed) and the main diagnosis will be evaluated. For this, the normality and homoscedasticity of the sample will be studied with Shapiro‒Wilk and Levene tests, respectively. Depending on the results, Student’s t test or ANOVA will be applied, depending on the number of groups, or the corresponding nonparametric tests. In addition, an analysis of paired measures will be carried out to analyze the evolution of the scores of the Barthel, Braden and Downton indices, what will serve us as a measure of diagnostic accuracy for our instrument, using these measurements as criteria. Categorical variables will be analyzed using the chi-square or Fisher’s exact test, and correlations will be studied with the Pearson or Spearman test, depending on the application conditions.

After this initial analysis, the cumulative incidence and period incidence of pressure injuries, falls and patients with functional loss will be estimated by unit and overall. A survival analysis will be carried out with pressure injuries, falls or functional loss as dependent variables and the other study variables as independent variables.

Next, the sensitivity, specificity, and positive and negative predictive values of the VALENF instrument will be analyzed to detect patients at risk of pressure injuries, falls, and functional loss using the Barthel, Braden, and Downton indices as reference tests. At this point, it should be considered that the protocolized prevention measures will be applied for those patients who are assessed to be at risk of pressure injury or fall to safeguard the ethical and deontological commitment of nonmaleficence. For this reason, this analysis will be carried out only with the positive cases first and, second, including the true positives with those other patients to whom the corresponding prevention measures were applied. We understand that this situation may bias the diagnostic accuracy results of the VALENF instrument, but we believe that it is a viable solution and that it can also provide information on the effectiveness of the measures used.

Finally, the VALENF instrument cutoff points will be established to detect the risk of pressure injuries, falls, and functional loss through simple linear regressions with the original instruments and cluster analysis to categorize patients. Moreover, and analysis of the area under the ROC curve will be carried out, considering acceptable values 0.7 to 0.8, excellent if 0.8 to 0.9, and outstanding if more than 0.9, and the Youden index will be used to calculate the optimal cut-off point [31]. A value of *p* < 0.05 will be considered in the comparisons of the hypotheses, and the statistical analysis will be carried out with SPSS v-25 and Jamovi v-2.3.2 software.

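### Functional loss is collected at discharge but analysed as a survival outcome, so its event time as written is length of stay; falls and pressure injuries need onset dates

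*Protocol article*

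**What the plan says.** The section Statistical analysis and diagnostic accuracy announces: "A survival analysis will be carried out with pressure injuries, falls or functional loss as dependent variables and the other study variables as independent variables". It names no model, time origin or event date. Cumulative and period incidence are listed as a separate step before it.

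Variables and instruments lists "outcome variables that necessitate nursing care, such as falls, pressure injuries, and functional loss". Functional loss is defined there only by a citation, and no date of onset appears for any of the three outcomes. Data collection fixes when they are gathered: "the outcome variables sensitive to nursing care will be collected at the time of discharge".

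The same section says that the ward nurses "will carry out the recruitment, data collection and follow-up during the hospitalization of the patients included in the study prospectively". It gives the instrument schedule twice. VALENF, Barthel, Braden and Downton "will be employed upon admission, every five days, and upon discharge". A later sentence reads: "The patients will be assessed upon admission, at five days, and upon discharge".

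On length of stay, Participants and sample says only that eligible patients "are expected to stay longer than 48 h". The article gives no mean stay and no expected incidence.

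On the predictors, the Background says that "the VALENF instrument has a high predictive capacity on the Barthel" index, with adjusted R² 0.938, and gives 0.926 for Braden and 0.921 for Downton.

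**The concern.** A survival analysis needs a time at which the event happened. If functional loss is noted when the patient leaves, the only time available is the discharge day. Patients without loss are censored on their own discharge day. Both kinds of time are then length of stay, and the model compares how quickly patients are discharged with loss, not how quickly they lose function. Frailty, comorbidity or a medical admission could lengthen stay and so appear to protect against functional loss.

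Falls and pressure injuries do have a natural onset date. If that date is not captured, the same problem applies to them. If it is captured, discharge still ends the period in which an in-hospital event can occur, and that matters for any curve of cumulative risk.

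A further point concerns the predictors. Read literally, the other study variables include VALENF and the three indices it was built to reproduce.

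**Working it through.** The article gives no figure for the survival analysis that could be reproduced. Its one sample size, 521, rests on a paired comparison of proportions. All stays, hazards and incidences below are therefore assumptions that show a mechanism.

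**1. Algebra for discharge-dated loss.** Let d be the daily discharge hazard (1/mean stay) and h the daily hazard of losing function. Among patients still in hospital on day t, the hazard of being discharged with loss is d × (1 − exp(−ht)). If two groups share the same h, their hazard ratio is d₁/d₀ at every t. For mean stays of 12 and 6 days this is (1/12)/(1/6) = 0.50, although the true effect on onset is nil.

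**2. Simulation with equal onset hazard.** Inputs: 40,000 patients, h = 0.03 per day in both groups, mean stays of 6 and 12 days, Cox model, true hazard ratio 1. A single cohort was run, then 12 further cohorts of the same design to remove simulation noise.

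| How the event is dated | HR, single cohort | HR, mean of 12 |
|---|---|---|
| True date, censored at discharge | 0.95 | 1.00 |
| Next five-day visit, or discharge if earlier | 0.78 | 0.82 |
| Discharge day | 0.48 | 0.50 |

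The risk of loss by discharge is h/(h + d): 0.03/(0.03 + 0.167) = 15% for short stays and 0.03/(0.03 + 0.083) = 26% for long stays. The long-stay group thus has the same daily hazard and a higher risk per stay, yet the discharge-dated model reports half the hazard. It is wrong for either question.

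**3. Simulation with equal risk per stay.** With the risk of loss fixed at 30% in both groups, discharge dating gives HR 0.67 for mean stays of 6 versus 9 days and 0.49 for 6 versus 12. A separate run with 469 patients, 25% loss in both groups and the stay beyond 48 h doubled gave a Cox HR of 0.49 and a logistic odds ratio of 0.99.

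**4. How far five-day visits help.** Suppose stay is 2 days plus an exponential time, with overall mean m. The share leaving by day 5 is 1 − exp(−3/(m − 2)): 63%, 45% and 31% for m = 5, 7 and 10. These patients have essentially only admission and discharge scores. Under the second schedule sentence, nothing is measured between day 5 and discharge for anyone.

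**5. Falls and pressure injuries.** The first row of the table shows that censoring at discharge is sound for the hazard ratio when true dates exist. Cumulative risk is different. Assume 5% in-hospital incidence and a mean stay of 7 days. The daily hazard is 0.05 × (1/7)/0.95 = 0.0075. One minus Kaplan-Meier at day 14 is 1 − exp(−0.0075 × 14) = 10.0%, against a cumulative incidence of 4.4%.

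**6. Predictors.** The variance inflation factor is 1/(1 − R²): 1/0.062 = 16.1, 1/0.074 = 13.5 and 1/0.079 = 12.7. Standard errors would grow by the square root, about 4.0, 3.7 and 3.6 times. This applies only if VALENF and an index enter one model, and only if the reported R² describes VALENF in the form entered.

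**The case against.** The article does not say that outcomes are collected only at discharge. It uses that restriction for the admission variables, follow-up is prospective, and a discharge form may well carry the date of a fall or injury. A condensed article may leave such fields to the case report form. This stands, so a reader should not conclude that the dates will certainly be missing.

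Serial Barthel scores could date functional loss to within an interval. This stands in part. The article does not say they will be used so, the two schedule sentences disagree, and five-day dating reduces the bias without removing it.

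Equal risk per stay with a doubled stay implies a lower daily rate, so HR 0.49 in that setting could be called a choice of estimand. That is fair for step 3. It does not touch steps 1 and 2, where the onset hazard is equal and the ratio is still about 0.5.

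A reader might also infer that discharge as a competing event invalidates the analysis of falls and injuries. The documents do not support this. Censoring at discharge is valid for cause-specific hazards, nowhere does the article plan to report one minus Kaplan-Meier as risk, and incidence is listed separately.

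Finally, the article does not say that all variables enter one joint model; separate models fit its wording equally well.

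**Conclusion.** The point holds for functional loss. Followed as written, the survival analysis uses length of stay as event time and biases the hazard ratio of any factor related to stay: about 0.5 for a doubled mean stay with no true effect, and about 0.8 with five-day dating. The direction follows from the algebra; the sizes rest on assumed stays and hazards. The definition of functional loss, given only by citation, is taken here as one settled at discharge.

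For falls and pressure injuries the point is narrower. Onset dates should be assured, and cumulative risk over time, if reported, must allow for discharge. The collinearity point is a caution about how the sentence on predictors is carried out, not a demonstrated error.

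To call the whole survival analysis invalid would go too far. It is secondary: the planned sensitivity, specificity, predictive values, ROC areas and cut-off points do not depend on it.

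**What to change.** - Analyse functional loss, discharge versus admission, by logistic or modified Poisson regression. This answers who leaves with loss, not how fast it occurs. If timing is wanted, use an interval-censored model on the serial Barthel scores, after reconciling the two schedule sentences in Data collection.
- Make sure REDCap holds the date of first fall and the date of first new pressure injury. Fit cause-specific models from admission, censored at discharge, death or transfer.
- If cumulative risk over time is reported, treat discharge, death or transfer as competing events (Aalen-Johansen estimator), not as censoring in one minus Kaplan-Meier.
- Fit VALENF and each index in separate models, each with a short fixed set of covariates, for example age, Charlson index and type of process.

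The cost is at most two date fields and a few sentences of analysis text. The binary analysis of functional loss needs no new data. The downside is fewer covariates in each model.

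### The accuracy analysis labels its function target as risk of functional loss, but the only reference named is the Barthel Index, which the objective treats as a measure of present functional capacity

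*Protocol article*

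**What the plan says.** The Background (Protocol article) describes three components: "This meta-tool integrates the assessment of functional capacity, the risk of pressure injuries and the risk of falls". Only the last two are called risks. The Abstract and the main objective at the end of the Background use the same three terms. The Abstract then names Barthel, Braden and Downton in the matching order, so Barthel is the function instrument.

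The target changes within the Background itself, which says that "its sensitivity, specificity, and predictive values for detecting patients at risk of functional loss, pressure injuries, or falls remain to be determined". Statistical analysis and diagnostic accuracy keeps the changed target. VALENF's accuracy is to be studied "to detect patients at risk of pressure injuries, falls, and functional loss using the Barthel, Braden, and Downton indices as reference tests", and its "cutoff points will be established to detect the risk of pressure injuries, falls, and functional loss". The article says that these thresholds are to be set "through simple linear regressions with the original instruments and cluster analysis to categorize patients". A ROC analysis with the Youden index follows, with no statement of which condition it classifies.

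Functional loss also has a place of its own. Variables and instruments lists "outcome variables that necessitate nursing care, such as falls, pressure injuries, and functional loss", apart from the index and reference tests. Data collection says that "the outcome variables sensitive to nursing care will be collected at the time of discharge", while VALENF and the three indices "will be employed upon admission, every five days, and upon discharge". The statistical section assigns observed functional loss to incidence estimates and to a survival analysis. It does not name it as the reference for sensitivity, specificity or cut-offs.

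**The concern.** Being at risk of functional loss is a statement about the future. A Barthel score taken alongside VALENF describes the patient on that day. If the Barthel level is the criterion, a low score makes the patient reference-positive because function is already reduced. A patient who is independent on admission and declines before discharge is reference-negative, and a low-risk VALENF result in that patient counts as correct.

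This is a mismatch in the target condition, so better agreement between the two instruments does not remove it. The Background reports an adjusted R² of 0.938 for VALENF on Barthel, so a high accuracy figure is likely. At stake is what one of the three accuracy results, and the cut-off derived with it, may be said to show.

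**Working it through.** The plan gives no figure for this point, so there is none to reproduce. The check sets the statements side by side and then illustrates the gap with assumed rates.

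**Comparison of statements**

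| Item | Protocol article | Nature |
|---|---|---|
| Function component (Abstract; Background) | functional capacity | present state |
| Accuracy target (Background; statistical section) | risk of functional loss | future event |
| Named reference (statistical section) | Barthel, with Braden and Downton | measured on the same occasions as VALENF |
| Observed functional loss (Variables; Data collection) | separate outcome, recorded at discharge | the event itself |
| Named use of observed loss (statistical section) | incidence, survival analysis | no sensitivity, specificity or cut-off |

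The second and third rows do not match, and the variable that would match the second row is not used as the accuracy reference.

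**Illustration 1: a test identical to Barthel.** Let p be the share of patients who are Barthel-positive on admission and r the ratio of later loss rates, positive to negative. Both are assumptions. Sensitivity against Barthel is 100%. The share of later losses that the test flags is

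p·r / (p·r + 1 − p)

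- p = 0.30, r = 0.5: 0.15 / 0.85 = 0.176
- p = 0.30, r = 1: 0.30 / 1.00 = 0.300
- p = 0.30, r = 2: 0.60 / 1.30 = 0.462
- p = 0.20, r = 0.5: 0.10 / 0.90 = 0.111
- p = 0.40, r = 2: 0.80 / 1.40 = 0.571
- p = 0.40, r = 4: 1.60 / 2.20 = 0.727

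At r = 1 the formula returns p. The answer is driven by the assumed r.

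**Illustration 2: near-perfect agreement.** Take N = 521 (Table 1) and assume VALENF agrees with Barthel dependence at sensitivity = specificity = 0.95. Ten combinations were computed, with 20% or 40% dependent on admission, later loss of 10% to 30% in independent patients and 10% to 40% in dependent patients. The two extremes for sensitivity are:

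- 20% dependent, loss 0.30 (independent) and 0.20 (dependent). There are 104.2 dependent and 416.8 independent patients. Losses: 104.2 × 0.20 + 416.8 × 0.30 = 145.9. Flagged losses: 104.2 × 0.95 × 0.20 + 416.8 × 0.05 × 0.30 = 26.1. Sensitivity for loss: 26.1 / 145.9 = 0.18.
- 40% dependent, loss 0.10 (independent) and 0.30 (dependent). There are 208.4 dependent and 312.6 independent patients. Losses: 208.4 × 0.30 + 312.6 × 0.10 = 93.8. Flagged losses: 208.4 × 0.95 × 0.30 + 312.6 × 0.05 × 0.10 = 61.0. Sensitivity for loss: 61.0 / 93.8 = 0.65.

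Across all ten, against later loss, specificity is 0.56 to 0.81 and positive predictive value 0.10 to 0.39. Between 30 and 119 independent patients who decline would count as true negatives against Barthel.

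**The case against.** The strongest reply is that the study is one of concurrent accuracy. The main objective compares VALENF with the usual instruments, and the Abstract expects it to be at least as valid as they are. For a tool meant to stand in for Barthel, Barthel is the right comparator. This stands: the comparison is sound, and only the label and the claim drawn from it need changing.

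Second, the statistical section plans a paired analysis of how the three indices change over the stay and says this will serve as a measure of diagnostic accuracy. That hints at change in Barthel as a criterion. However, the sentence defines no decline and is not carried into the paragraphs on sensitivity, specificity or cut-offs, which name the indices themselves.

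Third, the survival analysis takes functional loss as a dependent variable with the other study variables as predictors, so VALENF may already be related to observed loss. That is useful, but it gives no accuracy measure and no cut-off.

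Fourth, the ROC step names no condition to classify, and the caveat about preventive measures suggests that observed events may play some part. That caveat is confined to pressure injury and falls. It does not settle the function target.

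A reader might go further and infer that the cut-off is certain to misclassify independent patients and that wards would then direct care away from them. The article does not support this. It gives no Barthel threshold, no time point and no ROC condition, and it describes no care pathway triggered by the function score. Likewise, that patients at the bottom of Barthel cannot lose further points holds only if functional loss means a fall in Barthel, and the article defines it only by citation.

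**Conclusion.** The point holds as a mismatch between the stated target and the named reference. It starts in the Background and is fixed in the statistical section. If the plan is followed as written, concurrent agreement with current function would be presented as detection of future loss, although the loss itself is recorded and available.

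This rests on the plain reading that the Barthel level, not its change, is the criterion. How individual patients would be classified remains an inference from that reading. The size of the gap cannot be derived from the article. The figures above show only that high agreement with Barthel is compatible with low to moderate sensitivity for later loss. Illustration 1 ran from 11% to 57% for p of 0.20 to 0.40 and r of 0.5 to 2, and reached 73% at p = 0.40 and r = 4. Neither illustration is an estimate for this study.

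**What to change.** 1. In the Background and in both accuracy paragraphs of the statistical section, label the Barthel-referenced target *functional capacity/dependence at the time of assessment*. Limit the VALENF-versus-Barthel accuracy and cut-off claims to that label.
2. For any claim about risk of functional loss, add a ROC analysis of admission VALENF, with admission Barthel as comparator, against the functional-loss outcome already collected at discharge. Restrict it to patients in whom the defined loss is possible, and state that definition beside the analysis.
3. If change in Barthel was meant as the criterion, say so in the accuracy paragraphs and define the change there.

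The cost is a change of wording and one further analysis on data already planned, with no new measurements. The result for functional loss will probably be less favourable than agreement with Barthel. It will also be less precise, because it depends on the number of events: at an assumed loss rate of 10%, 521 × 0.10 gives about 52 before any losses to follow-up.
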